### Depression

Depression will be assessed by the PHQ-9 adapted by the Stanford Patient Education Research Center [83, 84]. The nine-item scale assesses the presence and frequency of depressive symptoms over the past two weeks, yielding a score range of 0–27 where a score of 15 or greater is considered major depression, and 20 or more is severe major depression.

### Quality of life

Quality of life will be assessed using two instruments that describe a spectrum of quality of life outcomes. The LUP-QOL incorporates the Medical Outcomes Study (MOS) Short Form 36 Health Survey (SF-36) and the Functional Assessment of Chronic Illness Therapy-Fatigue (FACIT-F), which are reliable and valid instruments that are frequently used in quality of life studies of persons with lupus [85–87]. The questionnaire includes questions pertaining to physical function, role function, social function, mental health, health perception and pain.

### Neuroendocrine response to stress

Assessment of urinary catecholamine levels will require that the identified sub-sample of participants collect their own samples in a brown 24-h urine container with 30 mL 6 N hydrogen chloride (HCl) of urine collected and the date/time collection started and finished. Samples will need to be kept refrigerated between collections and then the completed container kept on ice until couriers pick up samples and bring them back to the lab for testing. Random subjects will be asked for an immediate additional collection to assess variability imposed by participant-specific factors. A 4–30 mL aliquot is necessary for analysis. Assessment of urinary catecholamines includes tests of urinary epinephrine, norepinephrine, and dopamine, which will be quantified using liquid chromatography/tandem mass spectrometry (LC/MS-MS) [88–90]. Once results are complete, they will be sent via Autofax.

### Disease indices

Possible disease activity will be assessed using SLAQ [91]. The Systemic Lupus Activity Measure (SLAM) is a physician-rated, 31-item instrument that assesses symptoms and objective findings in the month prior to evaluation, in nine organ systems and seven laboratory items [92, 93]. Individual items are rated on a scale from 0 to 3 based on severity and are scored positively only if directly attributable to SLE. The SLAQ is based on items from the SLAM that could be self-reported. It asks a single Patient Global Assessment (PGA) question about presence and severity of lupus activity over the past month, questions on 24 specific symptoms of disease activity including weight loss, fatigue, fevers, oral ulcers, malar rash, photosensitivity, vasculitis, other rashes, alopecia, lymphadenopathy, dyspnea, chest pain, Raynaud’s phenomenon, abdominal pain, paresthesia, seizures, stroke, memory loss, depression, headaches, myalgias, muscle weakness, arthralgias, and joint swelling, and a single Numerical Rating Scale (NRS) asking the patient to rate disease activity on a scale of 0–10 over the past three months with the 0 anchored by ‘no activity’ and 10 anchored by ‘most activity’. The patient is then asked to rate the most active day over the past three months. Likert responses with four response categories (no problem, mild, moderate, severe) are used for the PGA and specific symptom questions.

To assess use of prednisone, immunosuppressive agents, nonsteroidal anti-inflammatory drugs [NSAIDs], and/or hydroxychloroquine), participants will also be asked to provide a listing of concomitant medications they are taking, to include the name of the medication, dose, unit, frequency, route, start date, stop date, and whether the medication will be ongoing at the end of the study. To account for factors that may affect catecholamine observations, participants will also be asked to include alcohol, caffeine, illegal/street drugs, and alternative remedies.

### Behavior change

Stanford Patient Education Research Center Questionnaires assessing medical outcomes such as hospital visits, illness intrusiveness, and use of stress management techniques [70, 77–79] will be used to further assess adoption and maintenance. These are behavior change scales, modified from the Medical Outcomes Study, to determine if participants are practicing cognitive stress reduction (pain reduction) and non-cognitive (mental stress management/ relaxation) techniques. These scales also assess whether key behaviors concerning communicating with health care providers and health care utilization have changed. Additionally, participants will have the opportunity to rate the credibility of the intervention and their expectancy of improvement. Participants will also be asked to keep diaries of practice during the intervention period. The number of diaries returned and self-ratings of practice frequency will be used to estimate adherence to intervention techniques and practices.

### Sample size and power

There will be three study arms in the proposed study; (1) intervention, (2) set menu control, and (3) control. Due to the potential similarity in each arm, a cluster-random trial will be considered, which takes into account between-cluster variation [94]. Relevant intervention literature shows effect sizes varying from 30-80 % [26, 29, 31, 39, 42, 45, 46, 49–51], which will be adequate for the proposed sample size design. The study will evaluate the difference in disease indices, quality of life and perceived and biological indicators of stress between the intervention and control groups, as well as within each group according to individual levels of intervention participation. Therefore, estimated sample sizes are displayed in Table 1 under a variety of effect sizes and drop-out levels in order to obtain a 0.95 significance level and 0.8 power of study. Our target recruitment level will be 150 participants according to an 80 % power level, in an effort to capture smaller effect sizes. This will correspond to an approximate 45 % response rate (*N* = 336), which is well within response and participation in other studies among the MUSC lupus cohort. Based on these results there is good to adequate power for most analyses to make the proposed project feasible.

**Table 1 Tab1:** Estimated sample size calculations

Estimated sample sizes				
Effect size	0.4	0.6	0.7	0.8
Sample size per arm (No drop out)	51	23	18	14
Sample size per arm (10 % drop out)	86	38	28	22
Sample size per arm (15 % drop out)	91	41	30	23

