
### Evidence based prevention programs

A large body of evidence has shown that health-promoting programs in stress management have been successful in helping people improve their health practices and related health conditions [25]. Based on reviews of scientific literature, investigators have suggested that therapeutic interventions should be proposed to reduce psychological distress to improve quality of life and possibly moderate the evolution of chronic and unpredictable diseases like SLE [32]. Cognitive-behavioral stress management (CBSM) techniques have resulted in short-term improvement in pain, psychological function, and perceived physical function among persons with SLE [27]. Additionally, psychoeducation [33] and graded aerobic exercise [34] have been shown to be useful in the management of fatigue. Programs designed to reduce stress levels of chronically ill patients have also included support therapy, lifestyle interventions incorporating elements of yoga or other similar disciplines, and mini-sessions on depression, adaptive coping strategies, and body image [27–29]. Although there is no generally accepted self-management program available for SLE [16], two programs that have been shown to be successful in improving conditions in patients with arthritis are the Arthritis Self- Management Program (ASMP) and the generic Chronic Disease Self-Management Program (CDSMP). Each program incorporates six weeks of peer led sessions ranging in disease-specific and more general self-help content. Arthritis self-management education delivered by small-group, home study, computer, and Internet modalities have demonstrated significant improvements in health distress, self-reported global health, and activity limitation, with trends toward improvement in self efficacy and mental stress management [31, 35–57].

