### Barriers to participation

Despite the apparent need for help with multiple illness-related problems and evidence that some of these problems can be ameliorated with cognitive-behavioral interventions without adverse effect, several studies have emphasized the need to design interventions that address barriers to participation and curtail noncompliance [58–61], particularly for African-American patients. Practicing physicians continue to struggle with patient compliance, poor adherence to therapeutic regimens, and failure of patients to keep scheduled appointments. For example, Petri et al. (1991) found that physicians rated African-Americans as less globally adherent than whites (43.5 % versus 66.3 % adherent, respectively) [62].

Despite recommendations from numerous national agencies that self-management education complement medical care [25, 43–47], arthritis self-management education has reached a limited number of people. Many Arthritis Foundation chapters have had difficulty disseminating arthritis self-management education programs. Additionally, many vulnerable populations have not been included in study samples [40, 42, 45, 51, 63–66]. Compliance is also a persistent problem in standardized programs. One study reported that less than 50 % of a closed eligible population participated, even when Internet and small-group programs were offered repeatedly over many years [67], suggesting that interventions may not be reaching the largest portion of lupus cases. Self-selection of program components has not been explored as an approach to improve such trends, but better self-management outcomes have been documented when participants are able to choose/dictate the content and/or pace of the respective treatment/intervention program [68–71].

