## Methods/Design

### Study design

SPIRIT guidelines have been adhered to for the reporting of this protocol. As depicted in Fig. 1, IQAN is a three armed randomized, wait list controlled trial to compare a patient-centered ‘a–la-carte’ approach that offers subjects a variety of modes of interaction from which they can choose as many or few as they wish (IQAN intervention) to a ‘set menu’ approach. A unique ‘a-la-carte’ self-management program will be offered to 50 African-American lupus patients participating in an ongoing SLE Clinic Database Project at MUSC. A ‘set menu’ control group of 50 lupus patients will be offered a standardized chronic disease self-management program only, and a control group of 50 lupus patients will receive usual care (UC), void of intervention components. The intervention will be coordinated by an Intervention Coordinator, with assistance from local/MUSC Study Coordinators. The Intervention Coordinator will work with each participant in the intervention arm to create an individualized intervention plan (IIP). Each IIP will include 1–4 options, including a mail-delivered arthritis kit, addition and access to a listserv, participation in a support group, and enrollment in local self-management program(s). Due to the nature of the IIP, the proposed intervention will inherently vary by participant. To ensure intervention integrity, discrete components will follow written protocols and peer leaders will complete a standardized checklist for each session/encounter. The total number of study visits will depend on group assignment and intervention participation. The entire study is over a period of 2 years. Location will vary depending upon the randomly assigned intervention. Locations range from a home setting to a set community meeting location. We expect the proposed study to demonstrate that a unique intervention strategy can reduce disease activity and damage, as well as perceived and biological indicators of stress, while improving quality of life indicators in African-American lupus patients. Measures of psychosocial and neuroendocrine responses to stress and disease activity and damage indices are expected to be inversely related to participation in intervention activities. Indicators of quality of life are expected to be positively related to participation. Validated measures of stress, depression, and quality of life will be collected in all patients in each condition before and after intervention activities.

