### Randomization

Within a month of all signed informed consent forms and baseline assessments being returned, the Biostatistician or their graduate assistant (GA) will enter baseline data and randomly assign each participant to one of three study arms: (1) intervention, (2) set menu control, or (3) control, returning that information to the principal investigator (PI) and Intervention Coordinator. Randomization will be stratified according to level of education (i.e., high school diploma or greater vs no diploma), or employment (more than 30 h per week vs less than 30 h), or income (SSI vs ≤ 25,000 vs > 25,000), depending on the completeness of data provided by the MUSC Study Coordinator. Within a month of randomization, the Intervention Coordinator will contact 50 intervention arm participants and assess and record their intervention modes of choice. The intervention coordinator will provide URL for listserv, support group details, and coordinate mailing of arthritis kits as applicable. The Intervention Coordinator will then link interested intervention arm and all set menu control arm participants to CDSMP’s in their area. The GA will make courtesy calls to the 50 participants in the control group letting them know of their designation and when they can expect contact and next round of evaluation materials to be completed and returned for compensation.

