### Data analytic plan

#### Quantitative data analysis

Data will be entered immediately after specified collection points into an Excel worksheet that will be built upon after each collection point and imported into SAS for data manipulation. To minimize risks to confidentiality, all data will be de-identified by assigning a numeric code to each participant and labeling all materials corresponding to that participant with their unique identifier. Additionally, data files that include personal identifiers will be stored separately from signed consent forms in locked file cabinets that only the Principal Investigator will have access to. The basic experimental design and corresponding data analyses will represent a one-between subjects (intervention versus control and intervention versus set menu control) and one-within or repeated factor (pre, post, and follow up assessments) crossed factorial design, with multiple dependent outcome measures (disease activity and damage, perceived and biological indicators of stress, quality of life, and urine catecholamines). The multivariate (multiple qualitatively distinct measures at multiple times) approaches to repeated measures [95, 96], based on the general linear model or general linear mixed model, will be used to test for pre-post-follow up changes between the intervention group and the control groups, as well as for exploratory correlations with urine catecholamines. These approaches provide better description of longitudinal patterns for each dependent variable and they are easier to successfully implement and generally more powerful than the use of covariant models when multiple outcome measures are considered simultaneously [96]. *P* < 0.05 will be used to indicate statistical significance. The data from all randomized participants will be analyzed. Multiple imputations will be used to estimate missing data from dropouts and those participants who do not complete follow up evaluations. We will evaluate the first 12 months to address primary outcomes and exploratory analyses will be conducted after 12 months once participants are given the option to cross over. Basic descriptive statistics such as means, ranges, and standard deviations will be calculated and tabulated for quantitative data using SAS (SAS Institute, Cary, North Carolina). Project-specific frequencies and percentages will be presented as a recruitment diagram according to CONSORT guidelines.

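### The literature effect range behind the power statement gives no basis for power on the a-la-carte versus set-menu comparison

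*Protocol article*

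**What the plan says.** The Sample size and power section has one set of effect inputs. It reports that "Relevant intervention literature shows effect sizes varying from 30-80" per cent, tabulates sample sizes per arm for effect sizes 0.4 to 0.8, sets the target at 150 for a "0.95 significance level and 0.8 power of study", and ends by calling power good to adequate for most analyses. No separate effect size is given for any pair of arms.

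The Quantitative data analysis section names two between-subject comparisons, "intervention versus control and intervention versus set menu control", and adds that a P value below "0.05 will be used to indicate statistical significance". Study design describes the trial as comparing the a-la-carte approach with a set-menu approach. In that design a "control group of 50 lupus patients will be offered a standardized chronic disease self-management program only". Under Randomization, the coordinator will "link interested intervention arm and all set menu control arm participants to CDSMP" workshops, so the same programme is open to both active arms.

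On the evidence, the Background states: "Arthritis self-management education delivered by small-group, home study, computer, and Internet modalities have demonstrated significant improvements". It also states: "Self-selection of program components has not been explored as an approach to improve such trends".

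**The concern.** Intervention versus usual care asks whether offering the package helps. Only intervention versus set menu separates the novel element, choice, from access to a programme. For that contrast the relevant effect is the increment of a-la-carte over a standard programme. The effect range offered comes mostly from literature on standard programmes, so it describes a different quantity.

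A reader of the sample-size section could take the set-menu contrast as covered by the 150 target and the general power sentence. A non-significant result might then be read as showing that choice adds nothing, when the trial had limited power for a moderate increment.

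**Working it through.** **Where the range comes from.** The sample-size section cites references 26, 29, 31, 39, 42, 45, 46 and 49–51, ten in all. The Background sentence on arthritis self-management education cites 31 and 35–57. The overlap is 31, 39, 42, 45, 46, 49, 50 and 51, that is, 8 of 10. The references that Barriers to participation cites for participants choosing content or pace (68–71) are not among the ten.

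**Inputs.** 50 per arm (150 / 3); alpha 0.05, with the stated 0.95 read as 95 % confidence; power 0.80. Two-sided testing is assumed because sidedness is not stated. Effects are in SD units. Reading 30–80 % as 0.3–0.8 SD is an inference, supported by the scale of Table 1.

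**Table 1 reproduced.**
- No drop-out row (51 / 23 / 18 / 14). A paired or one-sample two-sided t-test at alpha 0.05 and power 0.80 gives 51.01, 23.79, 18.03 and 14.30, which truncate to the printed row. A two-arm t-test gives 99.08, 44.59, 33.02 and 25.52 per arm two-sided, and 77.97, 35.04, 25.94 and 20.03 one-sided. Neither matches.
- Drop-out rows. A two-sample one-sided z-test, n = 2 × ((1.645 + 0.842) / d)² / (1 − drop-out), rounded up, gives 86 / 39 / 29 / 22 at 10 % and 91 / 41 / 30 / 23 at 15 %. The printed rows are 86 / 38 / 28 / 22 and 91 / 41 / 30 / 23, so agreement is within one.
- The rows therefore appear to use different formulas. Ten per cent drop-out applied to 51 gives 51 / 0.9 = 56.7, not 86.

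**Detectable difference, a-la-carte versus set menu.** By the normal approximation, d = (1.960 + 0.842) × √(2/n). For n = 50 this is 2.802 × 0.200 = 0.56. For n = 50 × 0.85 = 42.5 it is 2.802 × 0.217 = 0.61. The t-test gives 0.57 and 0.61.

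**Power by assumed increment** (two-sample t-test, two-sided 0.05, single time point):

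| Increment (SD) | 50 per arm | 42.5 per arm |
|---|---|---|
| 0.2 | 17 % | 15 % |
| 0.3 | 32 % | 28 % |
| 0.4 | 51 % | 45 % |
| 0.5 | 70 % | 62 % |

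By the normal-approximation calculation, 80 % power would need about 393, 175 and 99 per arm at 0.2, 0.3 and 0.4.

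**Allowing for the planned longitudinal model.** The protocol states no correlation between baseline and follow-up, so r = 0.5 to 0.7 is assumed. Baseline adjustment multiplies the residual SD by √(1 − r²), which is 0.866 at r = 0.5 and 0.714 at r = 0.7. With 50 per arm the detectable difference becomes 0.566 × 0.866 = 0.49 and 0.566 × 0.714 = 0.40. Power is 21–28 % at 0.2, 40–55 % at 0.3 and 82–93 % at 0.5. With 42.5 per arm, power at 0.5 is 75–89 %.

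**The case against.** The sample-size section speaks of the intervention and control groups and of most analyses; it never states 80 % power for the set-menu contrast. That is fair. But if the range was meant for usual care only, the set-menu contrast has no power basis at all, although it is named and shares the same significance threshold.

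The cited studies are not shown. That their effects are against usual care is inferred from the Background; they could be within-group changes, which the paired-test pattern in Table 1 would fit. The overlapping references also cover home study, computer and Internet delivery. This limits what can be said about the size of the increment. It does not turn the range into an estimate of the benefit of choice.

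Four stronger readings are tempting and should not be drawn:
- **That 0.8 − 0.3 = 0.5 is the largest possible difference.** It is not a bound. The a-la-carte arm can combine one to four components and might exceed a single programme's effect. No mode is compulsory, and the Background reports under 50 % participation in one closed eligible population, so the set-menu effect could fall below 0.3.
- **That the difference must be smaller than either programme's effect.** An increment of 0.5 would exceed a set-menu effect of 0.3. It is smaller than the a-la-carte effect only if the set menu has some benefit.
- **That no plausible difference could be detected.** With baseline adjustment at the assumed correlations, 0.5 reaches 82–93 % with 50 per arm.
- **That the protocol plans to read non-significance as equivalence.** It says nothing of the kind; the risk lies in a reader's interpretation.

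The Safety monitoring section also recodes non-participants as controls, so 50 or 42.5 per arm may not be the numbers analysed.

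**Conclusion.** The concern holds in a limited form. The stated effect range supplies no basis for power on a-la-carte versus set menu, a comparison the protocol names, and the general power sentence should not extend to it. On a single-time two-sided t-test, 80 % power needs an increment of about 0.57 SD (0.61 after 15 % drop-out). With baseline adjustment at an assumed correlation of 0.5–0.7 and no drop-out, it needs about 0.49–0.40 SD. For increments of 0.2–0.3 SD, power stays at about 21–55 % even with that adjustment.

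These figures rest on 50 per arm, alpha 0.05 two-sided and a common SD scale. The true increment is unknown, so the finding is that adequate power is unsupported, not that the trial will fail to detect a difference.

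Table 1 should not be taken as sound for usual care either. At effect size 0.4 a two-arm comparison needs about 99 per arm, and 50 per arm gives about 51 % power on the same t-test.

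**What to change.** In Sample size and power:

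1. State that the 30–80 % range and Table 1 are not applied to intervention versus set menu.
2. Add a line for that contrast: with 50 per arm, two-sided alpha 0.05 and a single-time comparison, the detectable difference at 80 % power is about 0.57 SD (0.61 after 15 % drop-out), and power is about 17 %, 32 %, 51 % and 70 % at 0.2, 0.3, 0.4 and 0.5. If credit is taken for baseline adjustment, state the assumed correlation.
3. Restrict the concluding power sentence to the analyses it actually covers.
4. Recompute the no-drop-out row of Table 1 as a two-arm comparison, and use one formula and one stated sidedness for all rows.

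In the Data analytic plan, state that intervention versus set menu is interpreted from its estimate and confidence interval, and that a non-significant result is not read as equivalence.

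The cost is a few sentences and one corrected table. Enrolment does not change; Trial status already reports 153 randomised. The downside is a less favourable stated power, for the set-menu contrast and, once Table 1 is recomputed, for usual care at smaller effects.

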### Concomitant interventions

During the first intervention year, intervention arm participants will have the option of participating in a mail-delivered arthritis kit, addition and access to a listserv, participation in a support group, and/or enrollment in local self-management program(s). After one year, set menu controls and controls will be invited to participate in the same options that were originally extended to intervention participants. During the first intervention year, set menu control arm participants will not have the option of participating in a mail-delivered arthritis kit, addition and access to a listserv, or participation in a support group. Control arm participants will not have the option of participating in any of the four offered intervention modalities. None of the offered intervention modes are required.

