### Secondary outcome

Measures of psychosocial and neuroendocrine responses to stress and disease activity and damage indices are expected to be inversely related to participation in intervention activities. Indicators of quality of life are expected to be positively related to participation.

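### Table 1 is introduced as sizing the within-arm participation analyses at 80 % power, but it gives no basis for that power below an effect of about 0.8

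*Protocol article*

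**What the plan says.** The Sample size and power section of the protocol article names two kinds of analysis. One is the difference between intervention and control groups. The other is a difference "as well as within each group according to individual levels of intervention participation". The next sentence opens with 'Therefore' and introduces Table 1, with sizes "under a variety of effect sizes and drop-out levels", "in order to obtain a 0.95 significance level and 0.8 power of study". All three rows of the table are labelled as sizes per arm.

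The target follows: "Our target recruitment level will be 150 participants according to an 80 % power level", with the stated aim of detecting smaller effects. The paragraph ends: "Based on these results there is good to adequate power for most analyses to make the proposed project feasible".

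Three other places bear on the point:
- Secondary outcome relates outcomes to participation, for example "Indicators of quality of life are expected to be positively related to participation". It gives no levels or cut-points and does not restrict the relation to one arm.
- Concomitant interventions says of the first year: "Control arm participants will not have the option of participating in any of the four offered intervention modalities".
- Quantitative data analysis takes the first 12 months for the primary outcomes and treats later analyses as exploratory.

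**The concern.** The word 'Therefore' makes Table 1 the sizing for both kinds of analysis. A comparison of participation levels within an arm has about 50 patients in all, shared among the levels, so no level can hold a whole arm's number. If Table 1 does not describe that design, the section attaches an 80 % power calculation to analyses that it does not size. The gap is widest at the smaller effects used to justify 150 patients. Someone interpreting a within-arm result later would have no correct statement of what effect it could have detected.

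**Working it through.** **Inputs.** Arms of 50 (Study design). Effects 0.4, 0.6, 0.7 and 0.8, read as standardised differences, and power 0.80 (Sample size and power). The '0.95 significance level' is read as alpha = 0.05, consistent with the P < 0.05 that "will be used to indicate statistical significance" in Quantitative data analysis. Sidedness is not stated, so both are shown. The splits of an arm are assumptions, since the article gives none.

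**Step 1. What Table 1 contains.** No single formula gives the whole table.

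| Row | Printed | Calculation that matches, before rounding down |
|---|---|---|
| No drop-out | 51 / 23 / 18 / 14 | One-sample or paired t-test, two-sided: 51.0 / 23.8 / 18.0 / 14.3 |
| 10 % drop-out | 86 / 38 / 28 / 22 | Two-sample t-test, one-sided, divided by 0.90: 86.6 / 38.9 / 28.8 / 22.3 |
| 15 % drop-out | 91 / 41 / 30 / 23 | The same, divided by 0.85: 91.7 / 41.2 / 30.5 / 23.6 |

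The first row is a one-group size and the other two compare whole arms. None compares participation levels inside an arm.

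**Step 2. Power inside one arm, two levels.** For a two-sample t-test the noncentrality is d × √(n₁n₂/(n₁+n₂)) with n₁+n₂−2 degrees of freedom. For 25:25 this is d × √12.5 = 1.41 / 2.12 / 2.47 / 2.83. For 40:10 it is d × √8 = 1.13 / 1.70 / 1.98 / 2.26.

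| Split (assumed) | 0.4 | 0.6 | 0.7 | 0.8 | Effect at 80 % power (two-sided) |
|---|---|---|---|---|---|
| 25:25, two-sided | 28 % | 55 % | 68 % | 79 % | 0.81 |
| 25:25, one-sided | 40 % | 67 % | 79 % | 87 % | – |
| 40:10, two-sided | 20 % | 38 % | 49 % | 60 % | 1.01 |
| 21:22, two-sided (15 % drop-out: 50 × 0.85 = 42.5, about 43) | 25 % | 48 % | 61 % | 73 % | 0.88 |

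**Step 3. Participation as a continuous variable.** Convert with r = d/√(d²+4), giving 0.20 / 0.29 / 0.33 / 0.37. Power = Φ(atanh(r) × √(n−3) − 1.96). At n = 50 the first term is 1.36 / 2.03 / 2.35 / 2.67, so power is about 28 / 53 / 65 / 76 %. The correlation detectable with 80 % power is about 0.39, equivalent to d of about 0.84.

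**Step 4. Both active arms pooled.** The same formula with n = 100 gives about 50 / 83 / 92 / 97 %.

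**Step 5. The between-arm comparison, for reference.** With 50 against 50, two-sided power at 0.4 is about 51 %, and the effect with 80 % power is about 0.57. A two-sided comparison at 0.4 needs about 99 per arm before drop-out.

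**The case against.** The best defence is that the closing sentence promises good to adequate power for most analyses, not 80 % for each, and that the 80 % is attached to the recruitment target. A secondary analysis below 80 % does not contradict 'most'. This stands against reading the plan as guaranteeing 80 % for the within-arm analyses. It does not remove the sentence that offers Table 1 as the sizing for them.

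The splits are assumed, and an article may leave participation levels to the full protocol or analysis plan. That also stands, but an even split is the most favourable two-level case and the continuous version gives much the same result. One-sided testing raises the figures and essentially reaches 80 % at 0.7, yet it remains short at 0.4 and 0.6. It could also be said that groups of 25 exceed the first row's 23, 18 and 14. That row is a one-group size, so it does not apply to a comparison of two levels.

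A reader might go further in four ways, none of which the document supports:
- **That no power exists within an arm.** With an even split and no drop-out it is about 80 % at an effect of 0.8, which is a column of Table 1.
- **That the whole secondary outcome is underpowered.** The Secondary outcome section does not confine the relation to one arm, and pooling the active arms does considerably better.
- **That 'within each group' is impossible for controls.** This is true only of the first year; afterwards controls may build their own plan.
- **That a null within-arm result would be taken to show that participation does not matter.** Nothing in the article says so.

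**Conclusion.** The point holds for the within-arm clause of the sample-size section. Table 1 is introduced as sizing those analyses at 0.8 power, and no row does. In one arm of 50, the best-case two-sided power is about 28 % at 0.4 and 68 % at 0.7, and it approaches 80 % only at about 0.8. Uneven splits and drop-out lower it. The size of the gap rests on standardised effects, alpha of 0.05, a single-endpoint test and the assumed splits; the planned repeated-measures models could shift the exact figures. That no row of Table 1 is a within-arm size does not depend on those assumptions. A related fault in the same table is that its first row is not a between-arm size, so correcting only the participation clause would leave the paragraph misleading.

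**What to change.** In Sample size and power:
- State that Table 1 and the 80 % figure do not cover the within-arm participation analyses.
- Give their detectable effect with 50 per arm: about 0.8 with an even split and about 1.0 with an assumed 40:10 split, larger with drop-out.
- Say that they will be reported as exploratory estimates with confidence intervals, and that in the first year they apply only to the intervention and set-menu arms.
- In the same edit, correct the between-arm statement: the no-drop-out row is a one-sample or paired size, and 50 per arm gives about 51 % two-sided power at 0.4, with a detectable effect of about 0.57.

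This takes a few sentences and a corrected table row. Enrolment is unaffected, which matters because Trial status reports 153 already randomised. The cost is a less favourable statement of power.
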